## Abstract

**Introduction:**

Emerging evidence supports mindfulness as a potential psychotherapy for post-traumatic stress disorder (PTSD). Individuals with subthreshold PTSD experience significant impairment in their daily life and functioning due to PTSD symptoms, despite not meeting the full diagnostic criteria for PTSD in DSM-5. Mindfulness skills, including non-judgmental acceptance, attentional control and openness to experiences may help alleviate PTSD symptoms by targeting characteristics such as intensified memory processing, dysregulated hyperarousal, avoidance, and thought suppression. This trial aims to test the effects of mindfulness-based cognitive therapy (MBCT) when compared to an active control.

**Method and analysis:**

This 1:1 randomised controlled trial will enroll 160 participants with PTSD symptoms in 2 arms (MBCT vs. Seeking Safety), with both interventions consisting of 8 weekly sessions lasting 2 h each week and led by certified instructors. Assessments will be conducted at baseline (T0), post-intervention (T1), and 3 months post-intervention (T2), with the primary outcome being PTSD symptoms measured by the PTSD checklist for DSM-5 (PCL-5) at T1. Secondary outcomes include depression, anxiety, attention, experimental avoidance, rumination, mindfulness, and coping skills. Both intention-to-treat and per-protocol analyses will be performed. Mediation analysis will investigate whether attention, experimental avoidance, and rumination mediate the effect of mindfulness on PTSD symptoms.

**Discussion:**

The proposed study will assess the effectiveness of MBCT in improving PTSD symptoms. The findings are anticipated to have implications for various areas of healthcare and contribute to the enhancement of existing intervention guidelines for PTSD.

**Trial registration number:**

ChiCTR2200061863.

**Supplementary Information:**

The online version contains supplementary material available at 10.1186/s12888-024-05840-x.

## Introduction

Post-traumatic stress disorder (PTSD) is a psychiatric condition triggered by experiencing or witnessing a traumatic event [1]. Some examples of traumatic events are sexual assault, domestic violence, childhood abuse, serious injury, illness, transportation accidents, natural disasters, or any stressful events that threaten personal lives or those of their close ones [2]. The major symptoms of PTSD include flashbacks of traumatic events, sleep disturbance, nightmares, rumination, negative thoughts, avoidance, and dysregulated hyperarousal [3]. While exposure to trauma is common, only a minority will develop and meet the full diagnostic criteria of PTSD [4]. Subthreshold PTSD refers to the condition in which only part of the symptoms are present clinically. While this condition does not fulfill the diagnosis of PTSD, it is found to be more prevalent in the community [4]. A study in 2014 conducted across 24 countries found that while 3% of participants met the diagnostic criteria of DSM-5 for PTSD, there was an additional 4.6% that met the criteria of subthreshold PTSD [4]. In general, these people experience symptoms that are less intense than full PTSD. However, their impairment is still significant to well-being and everyday life [5]. Zlotnick et al. found no significant differences in terms of functional impairment between patients with full PTSD and subthreshold PTSD, suggesting that people with subthreshold PTSD could experience negative impacts comparable to that of a full PTSD condition [6]. Other studies showed diminished social and family functioning [7], more days of absence from work [8], and a greater risk of suicidal ideation among subthreshold PTSD patients [9]. Besides, co-morbidity of mental health disorders, such as eating disorders, major depressive disorder, general anxiety disorder, and substance abuse are common among individuals with subthreshold PTSD [10]. Yet, some studies found that veterans with subthreshold PTSD did not utilize mental health services more than those with no PTSD, despite their significant impairment [11]. Another study on elderly with subthreshold PTSD found that they were more likely to perceive the care they received as inadequate [12]. These suggest that subthreshold PTSD might be easily overlooked by clinicians. Hence, subthreshold PTSD should be considered a condition that requires clinical attention and intervention.

Hong Kong is a multi-cultural society located in the southern part of China. In recent years, the COVID-19 pandemic and social unrest have adversely impacted the mental health of Hong Kong people [13]. Concerns have been raised mostly over major depressive disorder and PTSD [14, 15]. A survey based in Hong Kong conducted before the pandemic in 2014 revealed that 2.9% of participants developed current probable PTSD [16] The overall prevalence of experiencing trauma directly (i.e. responded happened to me on Life Event Checklist ) was 64.8%, while the rate increased further to 88.7% when indirect exposure is included (i.e. witnessed it or learned about it on Life Event Checklist) During the social unrest in 2019, the prevalence of suspected PTSD rose to 12.8% [17], and it increased further to 28.6% during the COVID-19 period in 2020 [18]. Such an increase in subthreshold PTSD was also found across different populations and cultures, which might be due to the COVID-19 pandemic around the globe [19–21]. With its increasing prevalence and the significant impairment it brings, subthreshold PTSD has become a global health problem that requires attention from both Hong Kong and the international community.

Most guidelines recommend manualized trauma-focused psychotherapies as the first-line treatment for PTSD [22]. On the other hand, medications could be used to assist treatment of PTSD symptomology [22]. Recommendations for PTSD medications might differ across guidelines [23]. In general, SSRIs outperform other medications and their efficacy has been evaluated in several studies [24]. However, meta-analysis studies found pharmacological intervention not as effective as psychotherapy [25]. A manualized psychotherapy contains guided standards for psychologists or psychiatrists to follow while ensuring that all trauma topics are well addressed. Over the years, several psychotherapeutic approaches have been developed to target PTSD. Examples are narrative exposure therapy, cognitive reprocessing therapies, eye-movement systematic desensitization and reprocessing and cognitive-behavioural therapy [22]. Psychotherapies mainly focus on the re-processing of traumatic memories, psychoeducation of coping skills and emotional regulation [26]. Seeking Safety is an evidence-based manualized psychological treatment. Its protocol was developed by [name] in the early 2000s that targets PTSD and substance abuse [27]. The core idea of Seeking Safety is to establish “Safety”. The word “Safety” here is an umbrella term that contains multiple elements: reducing suicidality, establishing safe relationships, taking good care of self, maintaining healthy habits etc [28]. . The whole protocol of Seeking Safety consists of 25 topics. These topics covers cognitive, behavorial and interspersonal domains. Examples of topics are “Safety”, “Compassion”, “Honesty”, “Asking for Help”, “Commitment”, “Creating meaning” etc. However, therapists can personalise and select suitable topics in the treatment manual. Over the past 20 years, various studies have been conducted showing that Seeking Safety could reduce PTSD symptoms significantly among different populations [29–31]. While the above treatments are evidence-based and recommended for PTSD, several concerns have been raised in various studies. First, there remains a certain level of dropout rate in trauma-focused psychotherapy, with the pool dropout rate at 16% [32]. Potential reasons for dropout might be treatment intolerance and symptom exacerbation due to traumatic reminders [33]. Besides, some psychologists have expressed concern about trauma-focused psychotherapy as this approach requires patients to unveil their trauma to the therapist [34]. Moreover, most of them retain the residual symptoms with the persistent diagnosis of PTSD after therapy [35]. Therefore, more alternative approaches are needed for managing PTSD.

In recent decades, there has been emerging evidence that supports mindfulness practice in improving individuals’ well-being and improving the outcomes of mental health problems [36]. Mindfulness-based interventions have been used extensively in psychiatric practice to treat various mental health problems, including major depressive disorder, general anxiety disorder, insomnia, addiction, substance abuse and chronic pain [37]. The idea of mindfulness originated from Buddhism and was later popularised in the West by Kabat-Zinn and his colleagues [38]. It involves bringing an individual’s focus to the present moment with an emphasis on a non-judgemental attitude [39]. It also cultivates acceptance and compassion for one’s thoughts, feelings, and bodily sensations [40]. In psychiatric practice, mindfulness could be incorporated into different psychotherapeutic approaches. The most studied mindfulness-based interventions are mindfulness-based cognitive therapy (MBCT) and mindfulness-based stress reduction (MBSR). MBCT combines mindfulness with cognitive behavioural therapy techniques and was initially developed to combat recurring depression, while MBSR focuses on coping strategies for pain and stress under chronic health conditions [41]. Both interventions encourage participants to practise mindfulness daily by offering home practice, mainly formal and informal practices [42]. Formal practices are offered through audio-recordings with instructions while informal practices require participants to integrate mindfulness elements into everyday life [43]. Currently, both MBCT and MBSR are considered evidence-based treatments and are efficacious for various mental health problems and psychiatric symptoms [44].

The evidence available suggests mindfulness-based interventions as a potential intervention for PTSD. In 2013, Kearney et al. showed that MBSR significantly reduced PTSD symptoms among 47 veterans in a pilot randomised control trial [45]. Similarly, King et al. conducted another randomised control trial with 37 participants by comparing MBCT with a treatment-as-usual group in combating PTSD symptoms [46]. Results showed that MBCT participants demonstrated significant improvement in both avoidance symptoms and PTSD cognitions. Another study by Kim et al. conducted on 28 nurses found that a 60-minute semi-weekly mindfulness stretching could significantly reduce PTSD symptoms, compared to an exercise control group [47]. The effect persists even until 16 weeks post-intervention. A randomised control trial among veterans with a larger sample size (*n* = 116) found that MBSR could significantly improve PTSD symptoms, compared to a group of present-centered focused therapy [48]. Multiple mechanisms have been suggested to explain how mindfulness could potentially improve PTSD symptoms. According to the model suggested by Lang, mindfulness emphasizes non-judgemental acceptance, allowing individuals to re-process traumatic pasts without extreme mood alternations [49]. In addition, mindfulness promotes the ability to focus on present moments, which helps patients shift attention away from arousal symptoms and other trauma-related stimuli. Lastly, mindfulness reduces avoidance and thought suppression by promoting openness to experiences. Other studies suggest that mindfulness breathing and meditation exercises promote relaxation which relieves uncomfortable feelings brought by PTSD [50]. Besides, neurobiological evidence showed that mindfulness might improve functional connectivity in multiple brain areas among PTSD patients [51]. These areas include the default mode network, frontoparietal network and salience network. A study conducted among veterans revealed increased activity in the medial prefrontal cortex to fearful cues after receiving a mindfulness-based exposure therapy, which might enhance top-down regulation of the limbic system and improve hyperarousal and intrusion symptoms [52]. This evidence supports mindfulness-based intervention as an effective treatment for PTSD and subthreshold PTSD.

Although preliminary evidence is available, there is no definite conclusion on whether mindfulness should be adopted as a formal intervention for PTSD [37]. First, most studies that support mindfulness-based intervention lack active control. The intervention group is often compared to waitlist control or no control which did not account for non-specific effects such as improvement over time [51]. Second, these studies are mostly conducted within a certain target group (e.g. veterans, women, police) with a relatively small sample size which limits the generalisability of findings. To our knowledge, no studies have previously targeted community adults. Third, most of these studies were conducted in the West. The effect of mindfulness-based intervention on reducing PTSD symptoms among Eastern cultures remains in doubt and still requires further exploration. Fourth, most of these studies lack a comprehensive secondary analysis that helps explain the mechanism of how mindfulness could reduce PTSD symptoms. Most of the models proposed are still theoretical and lack support. Hence, a well-designed study with a larger sample size and better control is needed.

Here, we propose a randomised control trial to evaluate the effectiveness of MBCT in reducing PTSD symptoms among Chinese adults in Hong Kong. The intervention will be compared to an active evidence-based control, Seeking Safety. Participants will be recruited from various community sources.

### Objectives and hypothesis

#### Objectives

To evaluate the effectiveness of MBCT in reducing PTSD symptoms among Chinese adults in Hong Kong;To evaluate the effectiveness of MBCT in reducing depressive and anxiety symptoms, as well as promoting mindfulness and coping skills among Chinese adults with PTSD symptoms in Hong Kong;To evaluate if attentional control, experimental avoidance and rumination would mediate the effect of mindfulness on PTSD symptoms.

#### Hypotheses

MBCT is more effective in reducing PTSD symptoms when compared to Seeking Safety, the active control group;MBCT is more effective in reducing depressive and anxiety symptoms when compared to Seeking Safety, the active control group.Attentional control, avoidance and ruminative thoughts are the mediators of MBCT in reducing PTSD symptoms in MBCT.

## Methods

### Study design

This project is a two-arm randomised controlled trial that evaluates the effectiveness of MBCT compared to an active control group, Seeking Safety. Assessments will be made at baseline (T0), post-intervention (T1) and 3 months post-intervention (T2) [48]. A summary of the study design is displayed in Fig. 1.

**Fig. 1 Fig1:**
[figure not shown]
Flow of the proposed study. MBCT, mindfulness-based cognitive therapy

### Participants

Participants are Chinese adults aged 18 or above. They will be screened by the following inclusion and exclusion criteria. The inclusion criteria are (1) score 31 or above in the PTSD Checklist for DSM-5 (PCL-5), indicating the presence of significant PTSD symptoms [53], (2) PTSD symptoms must last for at least one month, and (3) If taking psychiatric medication, dosage must have been stable for 3 months. The exclusion criteria are (1) inability to understand Chinese, which is the language of all psychological sessions and materials, (2) possession of moderate to severe forms of diseases, either physical or psychological that renders participation in the study, and (3) previous participation in any structured mindfulness courses.

### Study setting and recruitment

This is a study with a multi-disciplinary collaboration including psychology, public health, psychiatry, and family medicine. Participants will be recruited from specialist psychiatric out-patient clinics, primary care clinics, psychiatry and clinical psychology departments of public hospitals of Hong Kong, community non-governmental organisations that provide psychiatric rehabilitation services and online support groups for patients with mental health disorders. Participants will either be referred by healthcare workers or apply via advertisements from these collaborators on a first-come-first-served basis. With reference to the inclusion and exclusion criteria, a primary screening will be done by a trained research assistant through telephone interviews. Those who pass the initial screening will meet a clinician to further confirm eligibility. Once eligible, a research assistant will further explain the procedures, study objectives and informed consent to the participants.

### Intervention: MBCT for PTSD

The intervention is MBCT with an established protocol utilised in prior studies for depression and anxiety. Minor adjustments are made to the protocol to tailor for the needs of trauma-sensitive individuals. The outline of the MBCT class is shown in Table 1. The MBCT is conducted in groups of up to 15 participants. It consists of 8 sessions with 2 h per week. Besides, to establish regular practices, a 45-minute homework per day is given to all participants. Audio recordings for home practice are provided and participants are suggested to document their practice through a given diary. Handouts and homework recordings are translated to Chinese by qualified health professionals, and are further face-validated by a group of expert mindfulness instructors. Instructors for MBCT are health professionals with formal training in mindfulness and certified to conduct MBCT. The training was referenced from the book, *Trauma-sensitive mindfulness: Practices for safe and transformative healing* [54]. This training will equip our instructors with the knowledge and skills to conduct mindfulness therapy for trauma-sensitive individuals. Several instructors instead of one will be recruited to ensure that the findings could be generalized.

**Table 1 Tab1:** Outline of MBCT program modified for this study

Session	Theme	Session content
Session 1	Awareness and Automatic pilot – identifying and stepping out of automatic pilot	Group orientation Ground rules and introduction Self-care: grounding & alert techniques to keep one in the window of tolerance, aware of own conditions, respect own limitations… Mindful eating: Raisin exercise and review Body scan practice and review
Session 2	Living in Our Heads	Body scan practice Practice and homework review Thoughts, feelings exercises with respect to PTSD symptoms Pleasant events calendar Sitting meditation
Session 3	Gathering the Scattered Mind	5-minute seeing or hearing meditation Lying down yoga stretches and review Home practice review Standing stretch and breath, body meditation, and review 3 Steps breathing space and review Unpleasant events calendar
Session 4	Recognizing Aversion	Sitting meditation and review 5-minute seeing or hearing meditation Practice and homework review Territory of PTSD and depression Breathing space and review Mindful walking and review
Session 5	Allowing/Letting Be – acceptance of one’s experience	Sitting meditation (working with difficulties) and review Read Rumi’s Guest House Practice and homework review 3 Steps breathing space and review
Session 6	Thoughts Are Not Facts – seeing thoughts as mental events	Sitting meditation (working with difficulties) Practice and homework review Moods and thoughts exercise: mood and thoughts related/alternative viewpoints exercise 3 Steps breathing space and review Discuss breathing space as the ‘first step’ before taking a wider view of thoughts Discuss relapse signatures (Respond Wisely I)
Session 7	“How Can I Best Take Care of myself?”	Sitting meditation (includes working with difficulties) Practice and homework review Explore links between activity and mood Plan how best to schedule such activities 3 Steps breathing space as the ‘first step’ before choosing whether to take mindful action Discuss participants’ relationship with PTSD symptoms Discuss informal meditations during everyday life 3 Steps breathing space or mindful walking
Session 8	Maintaining and Extending New Learning	Body scan practice Practice and homework review Course review Discuss ways to continue mindfulness meditation beyond this programme End the class with a concluding meditation

### Active control: seeking safety

Seeking Safety is a manualised psychoeducational protocol developed by [name] [27]. The Chinese Version of the handouts has been translated by a group of experienced clinical psychologists from New Life Psychiatric Rehabitation Association in Hong Kong. Seeking Safety is a group intervention with a size of up to 15 participants. There are 8 sessions with a total of 2 h per week. Eight among twenty-five topics are selected for the sessions. They are “PTSD: Taking Back Your Power”, “Safety”, “Detaching from Emotional Pain (Grounding)”, “Asking for Help”, “Honesty”, “Setting Boundaries in Relationships”, “Compassion”, and “Taking Good Care of Yourself”. The selected topics were discussed with [name] to ensure the inclusion of the essential cognitive, behavioral, and interpersonal components of Seeking Safety. To encourage commitment and application of coping strategies discussed during the therapy sessions, participants could utilise the “Safe Coping sheet” and “Commitment to recovery form” if they found needed. Instructors are mental health professionals who have passed the certification test of Seeking Safety. Several instructors will be recruited to conduct the session to ensure generalisability.

### Intervention fidelity

Intervention fidelity of MBCT will be assessed by an independent health professional who is a mindfulness training expert. He/she will be provided with a simplified checklist developed from the Mindfulness-based cognitive therapy adherence scale (MBCT-AS). The MBCT-AS is a 17-item measure that assesses the treatment adherence of therapists to standard MBCT [55]. All the sessions will be audio-taped and 15% of them will be screened by the mindfulness expert to assess compliance with the MBCT protocol.

### Randomization, concealment and blindness

Participants are randomised to either MBCT or Seeking Safety on 1:1 ratio. Randomisation is stratified by gender and psychiatric medication use. Randomisation results will be generated by an independent statistician with a computer and sequences are sealed in opaque envelopes by another research assistant who is not involved in the study. Participants will be informed by the research team of their allocated group based on the results in the sealed envelopes prepared beforehand. Participants will not be allowed to switch to another intervention group. Statisticians who analyse the results will be kept blinded from the group assignment.

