### Outcome measures

Demographic information will be collected at baseline, including their gender, age, education, income, marital status, medical history, medication, and types of traumatic events. Primary and secondary outcomes will be collected by a research assistant who is blinded to the group assignment at T0, T1 and T2 through questionnaires. In addition, participants from both groups will be asked to fill out a course evaluation at T1. Participants assigned to MBCT will fill out an extra section on their questionnaire indicating their mindfulness practice habits at T1 and T2. The primary and secondary outcome measures are shown below.

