### Primary outcome

PCL-5 score at T1 is the primary outcome of this study. PCL-5 has four subscales and each corresponds to one DSM-5 symptoms cluster in PTSD, including intrusion, avoidance, negative alternations in cognition and mood, and alternations in arousal and reactivity [56]. It is a self-report measure that reflects the PTSD symptoms severity of participants on a Likert scale from 0 to 4, ranging from “not at all” to “extremely”. A total score could be obtained by simply summing up all 20 items. Participants who score equal to or higher than 31 are considered to display significant symptoms [53, 57]. The Chinese Version of PCL-5 is translated by Fung et al. with good internal consistency and reliability [58].

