### Statistical analysis

Statistical analysis will be conducted by a statistician blinded to the group assignment of participants. The study results will be presented according to the Consolidated Standards of Reporting Trial 10 (CONSORT-10) standards. The mean, median, standard deviation (SD), interquartile range (IQR) and 95% confidence interval (95% CI) will be presented in the data description. The analysis of covariance (ANCOVA) will be the primary analysis for the primary outcome (PCL-5) and other secondary outcomes (i.e., PHQ-9, BAI, ACS, AAQ-II, RRS, FFMQ, SCSQ), with T1 score as the outcome and T0 score as the covariate. Both intention-to-treat and per-protocol analyses will be performed. For per-protocol analysis, participants who attend more than 4 classes will be considered to have satisfactory compliance. Effect size estimates will be obtained by comparing the T0 and T1 scores mean and SD, both between and within groups. For the secondary analysis, we will apply linear mixed model (LLM) to compare changes over time for PCL-5 score and other secondary outcomes between the intervention group and the active control group. Missing data will be incorporated into the LLM based on full information maximum likelihood. Mediation analysis will be done using the Baron and Kenny mediation method and structural equation modelling (SEM). The analysis will explore if the effect of mindfulness on PTSD symptoms is mediated by rumination, experimental avoidance and attentional control.

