### Sample size

G*Power (version 3.1.5) was used for calculating sample size. A previous study conducted on USA veterans with PTSD determined a between-group effect size of 0.59, comparing mindfulness-based intervention and present-centred therapy [48]. We hereby conservatively estimate the effect size of our study to be 0.5. Based on our previous studies on mindfulness-based intervention, we expect a 20% dropout rate at the end. Accounting for the dropout rate, and with a two-tailed $$\alpha$$error of 5%, 80% power, and 2 study groups, we will recruit 160 participants with 80 per arm.

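### The two factors that stratify the allocation are left out of the primary ANCOVA, which can make its standard error slightly too large

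*Protocol article*

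**What the plan says.** Under Randomization, concealment and blindness, the protocol article says "Participants are randomised to either MBCT or Seeking Safety on 1:1 ratio", and then "Randomisation is stratified by gender and psychiatric medication use". It does not say how balance within strata is obtained; no block size or other restriction is given.

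Under Statistical analysis, it says "The analysis of covariance (ANCOVA) will be the primary analysis for the primary outcome (PCL-5) and other secondary outcomes", and defines the model "with T1 score as the outcome and T0 score as the covariate". Neither stratification factor is named in the description of the ANCOVA, the linear mixed model or the mediation analysis. The Discussion mentions two further things that may enter the analysis, other interventions sought and mental health diagnoses. Neither is a stratification factor.

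Under Primary outcome: "PCL-5 score at T1 is the primary outcome of this study". Under Outcome measures, gender and medication are both on the list of baseline data: "Demographic information will be collected at baseline, including their gender, age, education, income, marital status, medical history, medication, and types of traumatic events".

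**The concern.** Stratified allocation makes the arms more alike on the chosen factors than simple randomisation would. If those factors predict the outcome, the sampling variance of the treatment difference falls. A model that leaves them out still counts their contribution as residual noise, so the standard error it reports is larger than the true one. Confidence intervals are then somewhat too wide, the test runs below its nominal 5%, and some power is given up.

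The same model is used for PCL-5 and for the seven secondary instruments, so the mismatch carries through all the T1 comparisons. The planned size gives just over 80% power by the sponsor's own calculation, so even a small gain that needs no new data is worth having.

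**Working it through.** **Inputs from the article.** Effect size: "We hereby conservatively estimate the effect size of our study to be 0.5". Error rates and size: "error of 5%, 80% power, and 2 study groups, we will recruit 160 participants with 80 per arm". Expected dropout is 20%.

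**Assumed inputs.** q, the share of the T1 variance left after T0 that gender and medication use explain, is not in the documents. It is taken as 3%, 5% and 10%, with 0%, 20% and 30% as outer values. Allocation is taken as balanced within strata and observations as independent.

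**Step 1: the plan's own figure.** A two-sample t-test with d = 0.5, two-sided alpha 0.05 and 80% power needs 64 per arm (power 0.801). Then 64 / (1 - 0.20) = 80 per arm, or 160 in total. The stated size reproduces and is not affected by this point.

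**Step 2: formulas for the model without the strata.**
- Reported SE / true SE = 1/sqrt(1-q)
- Actual alpha = 2 × [1 - Phi(1.96/sqrt(1-q))]
- Noncentrality at 64 per arm = 0.5 × sqrt(64/2) = 2.83
- Power without the strata = Phi((2.83 - 1.96)/sqrt(1-q))
- Power with the strata = Phi(2.83/sqrt(1-q) - 1.96)

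Example at q = 0.10: 1/sqrt(0.90) = 1.054, so the SE is 5.4% too large. The effective critical value is 1.96 × 1.054 = 2.07, which gives alpha = 0.039.

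| q (assumed) | SE too large by | Actual alpha | Power, T0 only | Power, T0 + strata |
|---|---|---|---|---|
| 0% | 0% | 5.0% | 80.7% | 80.7% |
| 3% | 1.5% | 4.7% | 81.1% | 81.9% |
| 5% | 2.6% | 4.4% | 81.4% | 82.7% |
| 10% | 5.4% | 3.9% | 82.0% | 84.6% |
| 20% | 11.8% | 2.8% | 83.4% | 88.5% |
| 30% | 19.5% | 1.9% | 85.0% | 92.2% |

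The gain from adjustment at 3%, 5% and 10% is 0.8, 1.3 and 2.6 points.

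**Step 3: simulation.** 160 participants, 20% random dropout and four strata. Assumed: prevalences of 70% and 50% for the two factors, T0-T1 correlation 0.5, and blocks of 4 within strata.
- T0-only alpha was 0.053, 0.044 and 0.040 at q = 0, 5% and 10%. With the strata in the model it was 0.052, 0.047 and 0.050.
- At q = 10% the T0-only model reported an SE of 0.154 against an empirical 0.147, a ratio of about 1.05. With the strata the two agreed at 0.146.
- Simulated power at q = 10% was 0.81 without and 0.84 with the strata.

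**Step 4: the same simulation with simple randomisation inside strata.** T0-only alpha stayed between 0.048 and 0.054 for every q, so the conservatism disappears. Adjustment still gained power at q = 10% (0.80 against 0.84).

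**The case against.** **The conditions are not in the documents.** Nothing says that either factor predicts T1 PCL-5 beyond T0, and no blocking is described. This stands, and it is why the result is stated conditionally. Stratifying has little purpose without some restriction within strata, so balance is the likelier reading, but it remains an inference.

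**Clustering may work the other way.** Both arms are delivered in groups of up to 15, and the analysis section has no group term. As an illustration only, assume 12 analysed per group and q = 5%. An intraclass correlation of 0.01, 0.02 or 0.05 gives a net alpha of about 2 × [1 - Phi(1.96/sqrt(1 + 11 × ICC - 0.05))] = 5.7%, 7.0% or 11%. This stands: a reader might infer that the trial's primary test is conservative overall, and the documents do not support that. The figures above isolate the effect of the omitted strata.

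**The power figures leave out T0.** They use the two-sample noncentrality, which treats 0.5 as the difference in units of the residual SD after T0. If 0.5 is instead the raw standardised difference and the T0-T1 correlation is 0.5 (assumed), T0-only ANCOVA already has about 90% power, and at q = 5% the strata add about 1 point. This stands and makes the gain smaller.

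**A condensed article may leave covariates to the analysis plan.** This carries little weight here. The article does not merely name ANCOVA; it writes the model out with its covariate, so a plan that added the strata would change the published model.

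**Conclusion.** The point holds in a limited form. The article stratifies on two factors and writes a primary model that leaves both out. If allocation is balanced within strata, the factors explain 3% to 10% of the variance left after T0, and observations are independent, the reported standard error is 1.5% to 5.4% too large, actual alpha is 4.7% to 3.9%, and adjustment adds about 1 to 3 points of power. If the factors do not predict the outcome, there is no effect.

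Three stronger readings are tempting and not supported:
- That the precision gained by stratifying is lost. The estimate keeps it; only the reported standard error fails to credit it.
- That the estimate is biased or false positives are inflated. This omission does neither.
- That dropout leaves a systematic imbalance in the strata. Chance imbalance among those seen at T1 adds random variation. Bias would need dropout to depend on arm and stratum together, which nothing in the article suggests.

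This is a small, inexpensive improvement to the primary model and not a threat to its validity.

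**What to change.** State that the ANCOVA for the primary and secondary outcomes includes gender and psychiatric medication use, with the values used at randomisation, as fixed covariates beside the T0 score. Add the same two terms to the linear mixed model. It would also help to state how balance within strata is achieved, since the size of the effect depends on it.

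The cost is one line of wording and two degrees of freedom if both factors are binary: with 128 analysed (2 × 64), the residual degrees of freedom fall from 125 to 123. No new data are needed, because both values must be known to randomise, and the sample size stays at 160. The change should be made before unblinding, so that the choice of covariates cannot be questioned later.

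It does not deal with clustering by therapy group. Because adding the strata makes the reported standard error smaller, the group question should be settled separately and not treated as answered by this change.
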